**4.6 Efficacy Assessment/Confirmation of Remission**

**4.6.1 Confirmation**

For non-randomized clinical studies with efficacy as the primary endpoint, the efficacy of PR and CR must be confirmed to ensure that the efficacy is not the result of evaluation error. This also allows for a reasonable interpretation of the results in the presence of historical data; however, the efficacy in the historical data of these trials should also be confirmed. However, in all other cases, such as randomized trials (Phase II or III) or studies with disease stability or disease progression as the primary endpoints, efficacy confirmation is no longer required, as it does not add value to the interpretation of trial results. Nevertheless, the removal of the requirement for efficacy confirmation makes central review to prevent bias even more important, especially in non-blinded experimental studies.

In the case of SD, there must be at least one measurement that meets the SD criteria specified in the protocol within the shortest time interval after the trial begins (generally no less than 6 to 8 weeks).

**4.6.2 Overall Response Duration**

Overall response duration is defined as the time from the first measurement that meets the criteria for complete response (CR) or partial response (PR), whichever is measured first, to the time of the first documented disease recurrence or progression (using the minimum recorded measurement in the trial as a reference for disease progression). Total complete response duration is defined as the time from the first measurement that meets the criteria for complete response (CR) to the time of the first documented disease recurrence or progression.

**4.6.3 Disease Stabilization Duration**

This is the time from the start of treatment to the time of disease progression (in randomized trials, this starts from the time of randomization), using the minimum total sum recorded in the trial as a reference (if the baseline total sum is the minimum, it is used as the reference for calculating disease progression). The clinical relevance of disease stability varies across different studies and diseases. If the proportion of patients maintaining the shortest duration of stable disease is used as an endpoint in a specific trial, the protocol should explicitly state the minimum time interval between the two measurements in the definition of SD.

Note: The duration of response, stable disease, and PFS are influenced by the frequency of follow-up evaluations after baseline assessment. The definition of standard follow-up frequency is beyond the scope of this guideline. Follow-up frequency should consider various factors, such as disease type and stage, treatment cycles, and standard protocols. However, if comparisons between trials are necessary, the limitations of the accuracy of these measurement endpoints should be considered.

**4.7PFS/TTP**

**4.7.1 Phase II Clinical Trials**

This guideline primarily focuses on the application of objective response as a study endpoint in Phase II clinical trials. In certain cases, the response rate may not be the optimal choice for evaluating the potential anticancer activity of a new drug/new regimen. In these cases, progression-free survival (PFS) or post-progression free survival (PPF) at the defined time point may be considered appropriate alternative indicators that provide the initial signal of the biological activity of the new drug. However, it is evident that in a non-controlled trial, these evaluations may be questioned, as seemingly valuable observations may relate to biological factors such as patient selection rather than the effect of the drug intervention. Therefore, a phase II clinical trial designed as a randomized controlled trial is best with these as study endpoints. However, the clinical presentation of certain tumors remains consistent (usually in poor condition), making non-randomized trials reasonable. In these cases, however, caution must be exercised in recording efficacy evidence when assessing expected PFS or PPF due to the lack of a positive control.

**Subsequent content includes phase III evaluation endpoints, independent assessments, result reporting, etc.; please refer to the English version for details.**

## Appendix III: Modified Criteria for Evaluation of Solid Tumor Efficacy

Since there is currently no official Chinese version of mRECIST, this is an internal translation; please refer to the English version for details.

Sections 1 and 2 mainly introduce the background knowledge (see the English version for details)

3. Measurability of the tumor at baseline level

3.1 Definition

At baseline level, tumor lesions/lymph nodes will be classified into measurable and non-measurable categories as defined below:

3.1.1 Measurable Lesions

Tumor lesions: At least one dimension that can be accurately measured (recorded as the maximum diameter), with a minimum length as follows:

- CT scan 10 mm (CT scan slice thickness not greater than 5 mm)
- Clinical routine examination instruments 10 mm (tumor lesions that cannot be accurately measured with measuring instruments should be recorded as non-measurable)
- Chest X-ray 20 mm
- Malignant lymph nodes: pathologically enlarged and measurable, a single lymph node's short diameter on CT scan must be ≥15 mm (recommended CT scan slice thickness not exceeding 5 mm). Only measure and follow up on the short diameter at baseline and during follow-up.

3.1.2 Unmeasurable lesions

All other lesions, including small lesions (longest diameter <10 mm or pathological lymph node short diameter ≥10 mm to <15 mm) and lesions that cannot be measured. Unmeasurable lesions include: meningeal disease, ascites, pleural or pericardial effusion, inflammatory breast cancer, cancerous lymphangitis of the skin/lung, abdominal masses that cannot be diagnosed and followed up by imaging, and cystic lesions.

3.1.3 Special Considerations Regarding Lesion Measurement

Bone lesions, cystic lesions, and lesions that have previously undergone local treatment need to be specifically noted:

Bone Lesions:

- Bone scans, PET scans, or plain films are not suitable for measuring bone lesions, but can be used to confirm the presence or disappearance of bone lesions;
- Lytic lesions or mixed lytic/sclerotic lesions with defined soft tissue components, and where the soft tissue components meet the aforementioned criteria for measurability, can be considered measurable lesions if these lesions can be evaluated using imaging techniques such as CT or MRI;
- Osteolytic lesions are classified as non-measurable lesions.

Cystic lesions:

- - - - Lesions that meet the definition criteria for a simple cyst in radiological imaging should not be considered malignant lesions solely due to their classification as simple cysts; they are neither measurable lesions nor non-measurable lesions.
      - If the lesions are cystic metastatic lesions and meet the aforementioned criteria for measurability, they can be considered measurable lesions. However, if there are non-cystic lesions present in the same patient, non-cystic lesions should be prioritized as target lesions.

Lesions that have undergone local treatment:

- - - - Lesions located in areas previously treated with radiotherapy or other local regional therapies are generally considered non-measurable lesions, unless there is clear progression of the lesion. The study protocol should detail the conditions under which these lesions are classified as measurable.

3.2 Measurement Method Description

3.2.1 Lesion Measurement

All tumor measurements in clinical evaluations must be recorded in metric units. All baseline assessments of tumor lesion size should be completed as close to the start of treatment as possible, and must be completed within 28 days (4 weeks) prior to the start of treatment.

3.2.2 Evaluation Methods

The same techniques and methods should be used for baseline assessment and subsequent measurements of the lesions. All lesions must be evaluated using imaging examinations, except for those lesions that can only be assessed through clinical examination.

Clinical lesions: Clinical lesions can only be considered measurable if they are superficial and have a diameter of ≥10 mm at the time of measurement (e.g., skin nodules). For patients with skin lesions, it is recommended to archive color photographs that include a ruler to measure the size of the lesions. When evaluating lesions using both imaging and clinical examinations, imaging should be preferred whenever possible, as it is more objective and can be reviewed repeatedly at the end of the study.

Chest X-ray: When tumor progression is an important study endpoint, chest CT should be prioritized, as CT is more sensitive than X-ray, especially for newly developed lesions. Chest X-ray detection is only applicable when the boundaries of the measured lesions are clear and lung ventilation is good.

CT, MRI: CT is currently the best available and repeatable method for efficacy evaluation. The definition of measurability in this guideline is based on CT scan slice thickness ≤ 5 mm. If the CT slice thickness is greater than 5 mm, the minimum lesion measurement should be at least twice the slice thickness. MRI may also be acceptable in certain cases (e.g., whole-body scans).

Ultrasound: Ultrasound should not be used as a measurement method for assessing lesion size. Due to its operator dependence, ultrasound lacks reproducibility after measurements are completed and cannot ensure consistency between different measurements in technique and measurement. If new lesions are discovered using ultrasound during the trial, confirmation should be done using CT or MRI. If considering the radiation exposure from CT, MRI may be used as an alternative.

Endoscopy and laparoscopy: These techniques are not recommended for objective evaluation of tumors, but they can be used to confirm complete response (CR) when obtaining biopsy specimens, and may be used to confirm recurrence in trials where the endpoint is CR followed by recurrence or surgical resection.

Tumor markers: Tumor markers cannot be used alone to evaluate objective tumor response. However, if the marker levels exceed the upper limit of normal at baseline, they must return to normal levels when evaluating complete response. Because tumor markers vary by disease, this factor must be considered when writing measurement standards into the protocol. Specific criteria for CA-125 response (recurrent ovarian cancer) and PSA (recurrent prostate cancer) response have been published. Additionally, the International Gynecologic Cancer Society has established CA-125 progression criteria, which will be incorporated into the objective tumor response criteria for first-line treatment of ovarian cancer.

Cytological/histological techniques: These techniques may be used to identify PR and CR under specific circumstances as outlined in the protocol (for example, residual benign tumor tissue is often present in lesions of germ cell tumors). When exudate may be a potential adverse reaction to a certain therapy (such as treatment with taxane compounds or angiogenesis inhibitors), and measurable tumors meet the criteria for response or disease stability, the occurrence or worsening of tumor-related exudate during treatment can be diagnosed using cytological techniques to differentiate between response (or disease stability) and disease progression.

4. Tumor Response Assessment

4.1 Assessment of All Tumors and Measurable Lesions

To evaluate objective response or potential future progression, it is necessary to conduct a baseline assessment of the total tumor burden for all tumor lesions, serving as a reference for subsequent measurement results. In clinical protocols where objective response is the primary treatment endpoint, only patients with measurable lesions at baseline are eligible for inclusion. Measurable lesions are defined as the presence of at least one measurable lesion. For trials where disease progression (time to progression or degree of progression at a fixed date) is the primary treatment endpoint, the inclusion criteria must clearly specify whether it is limited to patients with measurable lesions or if patients without measurable lesions can also be included.

4.2 Baseline Recording of Target and Non-Target Lesions

When there are more than one measurable lesions at baseline assessment, all lesions should be recorded and measured, with a total not exceeding 5 (no more than 2 from each organ), representing target lesions for all affected organs (that is, patients with only one or two affected organs may select a maximum of two or four target lesions for baseline measurement).

Target lesions must be selected based on size (longest diameter), capable of representing all affected organs, and measurements must demonstrate good reproducibility. Sometimes, when the largest lesion cannot be measured reproducibly, a new largest lesion that can be measured reproducibly may be selected.

Lymph nodes require special attention as they are normal tissue and can be detected by imaging even in the absence of tumor metastasis. Defined as measurable nodules or pathological lymph nodes that must meet the following criteria: CT measurement of the short diameter ≥ 15 mm. Only the short diameter needs to be measured at baseline. Radiologists typically use the short diameter of the nodule to determine whether it has metastasized. Nodule size is generally represented using two-dimensional data from imaging (CT uses axial planes, while MRI selects one plane from axial, sagittal, or coronal views). The minimum value is considered the short diameter. For example, a 20 mm × 30 mm abdominal nodule with a short diameter of 20 mm can be considered a malignant, measurable nodule. In this example, 20 mm is the measurement value of the nodule. Nodules with a diameter ≥ 10 mm but < 15 mm should not be considered target lesions. Nodules less than 10 mm do not fall within the pathological nodule category and do not need to be recorded or further observed.

The sum of the diameters of all target lesions calculated (including the longest diameter of non-nodular lesions and the short diameter of nodular lesions) will be reported as the baseline diameter total. If lymph nodes are included, as mentioned above, only the short diameter will be counted. The baseline diameter total will serve as a reference value for the disease baseline level.

All other lesions, including pathological lymph nodes, can be considered non-target lesions and do not need to be measured, but should be recorded during the baseline assessment. Records may indicate 'present', 'missing', or in very rare cases, 'definite progression'. Widely present target lesions may be recorded together with target organs (e.g., extensive pelvic lymphadenopathy or massive liver metastasis).

4.3 Response Criteria

4.3.1 Assessment of Target Lesions

Complete Response (CR): All target lesions disappear, and all pathological lymph nodes (including target and non-target nodules) must have a short diameter reduced to <10 mm.

Partial Response (PR): The sum of the diameters of target lesions must decrease by at least 30% from baseline levels.

Progressive Disease (PD): Referring to the minimum sum of the diameters of all measured target lesions throughout the study, an increase of at least 20% in diameter and relative increase is required (if the baseline measurement is the minimum, then the baseline value is used as a reference); In addition, the absolute increase in the sum of diameters must be at least 5 mm (the appearance of one or more new lesions is also considered disease progression).

Stable Disease (SD): The degree of reduction in target lesions does not reach PR, and the degree of increase does not reach PD levels, falling between the two; during the study, the minimum sum of diameters can be used as a reference.

4.3.2 Considerations for Target Lesion Assessment

Lymph Nodes: Even if the identified target lymph nodes decrease to less than 10 mm, the actual short diameter corresponding to the baseline must still be recorded during each measurement (consistent with the anatomical plane at baseline measurement). This means that if the lymph nodes are classified as target lesions, even if they meet the criteria for complete response, it cannot be said that the lesions have completely disappeared, because the short diameter of normal lymph nodes is defined as <10 mm. In the CRF form or other recording methods, target lymph node lesions must be specifically recorded in designated locations: for CR, all lymph node short diameters must be <10 mm; For PR, SD, and PD, the actual measured short diameter of the target lymph nodes will be included in the sum of the diameters of the target lesions.

Target lesions that are too small to measure: In clinical research, all lesions (nodular or non-nodular) recorded at baseline should be re-measured in subsequent assessments, even if the lesions are very small (e.g., 2 mm). However, sometimes they may be too small, resulting in images from CT scans being very blurry, making it difficult for radiologists to define exact values, and they may report it as 'too small to measure'. In such cases, it is very important to record the previous value on the CRF form. If the radiologist believes that the lesion may have disappeared, it should also be recorded as 0 mm. If the lesion is indeed present but is somewhat vague, making it impossible to provide an accurate measurement, it can be defaulted to 5 mm. (Note: The likelihood of lymph nodes exhibiting this situation is low, as they generally have measurable sizes under normal circumstances, or are often surrounded by adipose tissue, as in the retroperitoneal cavity; However, if such a situation arises where a measurement cannot be provided, it is also defaulted to 5 mm.)The default value of 5 mm is derived from the slice thickness of the CT scan (this value does not change with different slice thickness values of the CT). Since the likelihood of the same measurement value occurring repeatedly is low, providing this default value will reduce the risk of erroneous assessments. However, it must be reiterated that if the radiologist can provide the exact size of the lesion, even if the diameter is less than 5 mm, the actual value must be recorded.

Separated or combined lesions: When non-nodular lesions fragment into pieces, the longest diameter of each separated part is summed to calculate the total diameter of the lesion. Similarly, for combined lesions, they can be distinguished through the planes between the combined parts, and then the maximum diameter of each can be calculated. However, if the combination is inseparable, the longest diameter should be taken as the longest diameter of the fused lesion as a whole.

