**Key revisions in version 1.1 of RECIST**

The main revisions are:

Determination of the number of lesions: For the convenience of analysis, the evaluation of many trial data will be consolidated into a single database. According to this database, the total number of lesions required to assess the response endpoint tumor burden has been reduced from a maximum of 10 to a maximum of 5 (with a maximum of 5 per organ reduced to 2).

The determination of pathological lymph nodes is now consolidated to: nodules with a short axis value of 15 mm are considered measurable target lesions for evaluation. When assessing tumor efficacy, the short axis value of the (nodular) lesions must be included in the total sum of the lesions (radius). Nodules are considered normal when the short axis value shrinks to < 10 mm.

In clinical trials where response rate is the primary endpoint, efficacy needs to be confirmed; however, this is no longer necessary in randomized controlled trials, as the control group has become an effective means of interpreting trial data. The progression of the disease is elaborated in the following aspects: in addition to the original definition—an increase of 20% in the sum of target lesions (radius)—if the total number is very small, to prevent overestimation of the degree of deterioration, there must currently be an absolute increase of 5 mm in the short axis of the lesions. In addition, guidelines regarding the definition of 'definite progression' for non-measurable or non-target lesions are also provided—specifically, areas that may be confusing in the original RECIST guidelines. Finally, there is a section dedicated to the detection of new lesions, including an explanation of the FDG-PET scan results. Imaging Guidelines: The revised RECIST includes a new imaging appendix with updated recommendations for the best anatomical assessment of lesions.

Next Steps:

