**4.2 Baseline Recording of Target and Non-Target Lesions**

When there are more than one measurable lesions at baseline assessment, all lesions should be recorded and measured, with a total not exceeding 5 (no more than 2 from each organ), representing target lesions for all affected organs (that is, patients with only one or two affected organs may select a maximum of two or four target lesions for baseline measurement).

Target lesions must be selected based on size (longest diameter), capable of representing all affected organs, and measurements must demonstrate good reproducibility. Sometimes, when the largest lesion cannot be measured reproducibly, a new largest lesion that can be measured reproducibly may be selected.

Lymph nodes require special attention as they are normal tissue and can be detected by imaging even in the absence of tumor metastasis. Pathological lymph nodes defined as measurable nodules or target lesions must meet the following criteria: CT measurement of the short diameter ≥ 15 mm. Only the short diameter needs to be assessed at baseline. Radiologists typically use the short diameter of the nodule to determine whether it has metastasized. Nodule size is generally represented using two-dimensional data from imaging (CT uses axial planes, while MRI selects one plane from axial, sagittal, or coronal views). The minimum value is considered the short diameter. For example, a 20 mm × 30 mm abdominal nodule with a short diameter of 20 mm can be considered a malignant, measurable nodule. In this case, 20 mm is the measurement value of the nodule. Nodules with a diameter ≥ 10 mm but < 15 mm should not be considered target lesions. Nodules < 10 mm do not fall within the pathological nodule category and do not need to be recorded or further observed.

The sum of the diameters of all target lesions calculated (including the longest diameter of non-nodular lesions and the short diameter of nodular lesions) will be reported as the baseline diameter total. If lymph nodes are included, as mentioned above, only the short diameter will be counted. The baseline diameter total will serve as a reference value for the disease baseline level.

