All other lesions, including pathological lymph nodes, can be considered non-target lesions and do not need to be measured, but should be recorded during the baseline assessment. Records may indicate 'present', 'absent', or in rare cases, 'definite progression'. Widely present target lesions may be recorded together with target organs (e.g., extensive pelvic lymph node enlargement or massive liver metastases).

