**4.3.1 Efficacy Evaluation of Target Lesions**

Complete Response (CR): All target lesions disappear, and the short axis value of any pathological lymph nodes (regardless of whether they are target lesions) must be < 10 mm.

Partial Response (PR): A decrease of at least 30% in the sum of the diameters of all target lesions, relative to the baseline total diameter.

Disease Progression: An increase of at least 20% in the sum of the diameters of all target lesions, using the minimum diameter of lesions as a reference (including the baseline total diameter of lesions, if it is the minimum value). Additionally, in addition to the relative increase of 20% in the sum of diameters, the absolute value of the sum must also increase by at least 5 mm (Note: The appearance of one or more new lesions can also be considered disease progression).

Stable Disease (SD): Using the sum of the minimum diameters of lesions during the study as a reference, lesions that shrink do not meet the criteria for PR, and lesions that increase do not meet the criteria for disease progression.

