**4.3.2 Considerations for Evaluating the Efficacy of Target Lesions**
When the target lesion is a lymph node:

The actual short-axis measurement value should typically be recorded (in the same anatomical plane as the baseline measurement), even if all lymph nodes in the study regress to below 10 mm. This means that when the target lesion is a lymph node, even if the criteria for complete response are met, the sum of the diameters of the target lesions will not be 0, because lymph nodes with a short-axis value < 10 mm are defined as normal lymph nodes. Case report forms or other data collection methods may need to separately record nodular target lesions at the design stage; to determine whether there is a complete response, each nodule must achieve a short-axis value < 10 mm. For PR, SD, and disease progression, the sum of the target lesions (in diameter) will include the actual short axis values of the nodules.
Lesions that are too small to measure:

All lesions (nodular and non-nodular) recorded at baseline in the study must have their actual measurements documented in subsequent assessments, even if they are very small (e.g., 2 mm).

However, sometimes lesions or lymph nodes may be recorded at the threshold value because the signal is too weak during the CT scan, and the radiologist may be reluctant to provide an exact measurement, instead reporting it as 'too small to measure'.
It is important to record a measurement in the case report form when this situation occurs. If the radiologist believes that the lesion may disappear, the measurement can be recorded as 0mm. If the lesion is indeed present but the signal is too weak, it can be recorded as the default value of 5mm (this rule is not very applicable to lymph nodes, as normal lymph nodes have a clear size value and are often surrounded by adipose tissue, such as lymph nodes in the retroperitoneal cavity; However, if the lymph node is indeed present but the signal is too weak to measure, it can also be recorded as the default value of 5mm).

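### The mRECIST appendix tells readers to carry forward the previous value for a target lesion too small to measure, against its own 0 mm and 5 mm rules and against the RECIST v1.1 appendix

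*Protocol*

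**What the plan says.** Appendix III, 4.3.2 (Considerations for Target Lesion Assessment) covers a target lesion so faint on CT that the radiologist reports it as too small to measure. Its first instruction is "In such cases, it is very important to record the previous value on the CRF form". Three further rules follow in the same paragraph:

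- Lesion thought to be gone: "If the radiologist believes that the lesion may have disappeared, it should also be recorded as 0 mm".
- Lesion present but not accurately measurable: a default of 5 mm, justified there as lowering the risk of wrong assessments.
- Exact size obtainable: the actual value, even below 5 mm.

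Appendix II, 4.3.2, covers the same situation for RECIST v1.1. It asks only that a measurement be entered, then gives 0 mm for a lesion that may have disappeared and, otherwise, "If the lesion is indeed present but the signal is too weak, it can be recorded as the default value of 5mm". It contains no carry-forward.

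The ORR definition in Section 7.4 applies both criteria, with RECIST v1.1 as the primary one. Treatment ends for progression when RECIST v1.1 and mRECIST progression are both met (Protocol Summary, Research Process and Termination Criteria; Section 4.3.2).

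Two smaller slips lie nearby. Appendix II, 4.2, says "Widely present target lesions may be recorded together with target organs (e.g., extensive pelvic lymph node enlargement or massive liver metastases"), and Appendix III, 4.2, says nearly the same. Yet for measurable lesions chosen as targets, 4.2 says "all lesions should be recorded and measured, with a total not exceeding 5 (no more than 2 from each organ"), with the diameters summed. The Appendix II summary of key revisions says of progression that "there must currently be an absolute increase of 5 mm in the short axis of the lesions", whereas the definition in Appendix II, 4.3.1, says "the absolute value of the sum must also increase by at least 5 mm".

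**The concern.** A person completing the CRF cannot both carry the last value forward and enter 0 mm, 5 mm or the actual size. The carry-forward is worded as very important, while the 5 mm default is worded as permitted, so a literal reader could give the carry-forward priority.

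Response and progression are both computed from the sum of target diameters. A carried value hides any shrinkage since the previous scan. That can keep the mRECIST sum above the partial-response threshold. It also raises the smallest sum on record, which is the reference for progression. Images are read at the single centre (Section 9.3), so the local text matters, and a carried value cannot afterwards be told apart from a real measurement.

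**Working it through.** The protocol gives no figure to reproduce here: the sample size is fixed at 30 with no target ORR. The check therefore applies the protocol's own thresholds to assumed lesion sizes.

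**Inputs from Appendix III, 4.3.1.** Partial response: the sum falls by at least 30% from baseline. Progression: the sum rises by at least 20% over the smallest sum, and by at least 5 mm.

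**Assumed lesions.** Two targets, 40 + 20 = 60 mm at baseline. At follow-up the first is 36 mm and the second is too small to measure.

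Change = (36 + entry) / 60 - 1:

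| Entry for second lesion | Sum (mm) | Change | Time-point result |
|---|---|---|---|
| 0 mm | 36 | -40.0% | PR |
| 5 mm (default) | 41 | -31.7% | PR |
| 6 mm carried from an earlier scan | 42 | -30.0% | PR |
| 20 mm carried from baseline | 56 | -6.7% | SD |

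PR requires a sum of at most 0.70 × 60 = 42 mm, so in this example a carried value above 42 - 36 = 6 mm loses the response.

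**Progression, continuing the example.** The first lesion then grows from 36 to 45 mm, and the second keeps its entry.

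- 5 mm: 45 + 5 = 50 against 41, which is +9 mm and 50/41 - 1 = +22.0%. This is progression.
- 20 mm carried: 45 + 20 = 65 against 56, which is +9 mm and 65/56 - 1 = +16.1%. This is not progression.
- 6 mm carried: 45 + 6 = 51 against 42, which is +9 mm and 51/42 - 1 = +21.4%. This is progression.

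**Other assumed sizes, to show the range.**

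| Baseline (mm) | First lesion now | Carried value | Change, carried | Change, 5 mm | Change, 0 mm |
|---|---|---|---|---|---|
| 30 + 12 | 24 | 12 | -14.3% | -31.0% (PR) | -42.9% (PR) |
| 30 + 12 | 24 | 8 | -23.8% | -31.0% (PR) | -42.9% (PR) |
| 30 + 12 | 24 | 6 | -28.6% | -31.0% (PR) | -42.9% (PR) |
| 80 + 12 | 50 | 12 | -32.6% (PR) | -40.2% (PR) | -45.7% (PR) |

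For a single 10 to 20 mm target, carrying the baseline value gives 0%, against -50% to -75% with 5 mm.

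**Weight of one patient.** 1/30 = 3.3 percentage points of the mRECIST ORR. With assumed counts, 19/30 is 63.3% (Clopper-Pearson 95% CI 43.9 to 80.1) and 18/30 is 60.0% (40.6 to 77.3). A time-point flip changes ORR only if it changes the confirmed best response.

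**The case against.** The strongest reply is that the paragraph corrects itself. Its later rules cover every case (gone, present but unmeasurable, measurable) and leave none in which carry-forward is needed. Both appendices describe themselves as internal translations and point to the English versions, and the matching sentence in Appendix II has a measurement, so the previous value looks like a translation slip. That stands as an explanation of the origin, and it means bias arises only if a reader follows the sentence literally. It does not remove the contradiction: neither appendix says that the English text prevails.

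A reader might infer that the primary ORR is biased downward. The documents do not support this. RECIST v1.1 is the primary criterion, and its appendix lacks the instruction.

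A reader might also infer that all shrinkage of the lesion is lost. That is so only if the previous value is the baseline value. Scans are every 6 weeks (Section 6.3), and after an interim measurement the shrinkage up to that scan still counts.

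On the lumping sentence, a reader might infer a licence to leave target lesions unmeasured, including under RECIST v1.1. But it closes a paragraph about non-target lesions. The rules around it cap targets at two per organ, sum their diameters and require re-measurement, so it reads as a slip for non-target lesions.

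On the short-axis wording, a reader might infer shifted progression dates. It stands in a background summary, and the operative definitions in both appendices use the sum. No shift is shown.

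**Conclusion.** The contradiction in Appendix III, 4.3.2, is real and should be corrected. Followed literally, the sentence can turn an mRECIST partial response into stable disease (-31.7% against -6.7% in the main example) and can delay mRECIST progression (+22.0% against +16.1%). The latter also feeds the dual criterion under which treatment ends, so a patient could be progressing by RECIST v1.1 but not by mRECIST because of a data-entry rule alone.

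The reach is limited to the mRECIST readings and that dual criterion. Lesion sizes and responder counts are assumptions, not protocol figures, and some patterns give the same category whichever value is entered. The study is exploratory and sets no ORR threshold that a 3.3-point move could cross. Severity is minor to moderate; this is not a demonstrated bias in the primary endpoint. The lumping and short-axis sentences are minor wording corrections.

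**What to change.** In Appendix III, 4.3.2, replace *the previous value* with *a measurement*, and keep the 0 mm, 5 mm and actual-value rules directly after it, matching Appendix II, 4.3.2. Carry the same rule into the CRF completion guidance.

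As minor corrections:

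- In 4.2 of both appendices, change *target lesions* to *non-target lesions* in the sentence on recording widespread lesions together.
- In the Appendix II summary of key revisions, place the 5 mm absolute increase on the sum of diameters, as in 4.3.1 of both appendices.

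The cost is four wording changes and one line of CRF guidance. No extra scans, data or patients are needed. The change should be made before values are entered, because carried values cannot be identified later.
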